In this intervention, the counselor supervises fidelity, not content generation. The synchronous weekly mini session(s) serves to anchor and facilitate relational connection, provide developmental interpretation, and maintain clinical boundaries. To support this, counselors receive an auto-generated weekly summary of the student’s (a) micro-nudge delivery and engagement, (b) micro-coaching activity, and (c) reflective note submissions. The counselor’s task is not to manually “grade” or “correct” but to contextualize the AI-facilitated micro-work within the student’s authentic relational ecology, and to intervene if emotional distress or dysregulation emerges. Ultimately, this design upholds the core ethical framework that the AI augments the intervention dosage, but human counselors remain fundamental anchors of the developmental and relational process.

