Participation is voluntary, contingent upon the student’s willingness to engage in daily reflective micro-interactions for 8 weeks. Inclusion criteria are intentionally minimal to maximize ecological validity: must (a) possess sufficient functional literacy to interpret daily reflective prompts, (b) have access to a digital interface (e.g., mobile device), and (c) be available for one weekly 10–15 min synchronous mini-session with a counselor. Exclusion criteria are guided by safety and feasibility logic rather than clinical diagnostics. Students presenting with acute crisis indicators (e.g., active suicidal intent, imminent risk of harm, or major protective disclosure) are not enrolled into this model because such circumstances require immediate professional care with crisis protocols. The purpose of this design is not to triage or treat acute dysregulation but to examine whether an AI-supported PYD scaffold can be realistically implemented within an ordinary school setting.

To ensure participant safety, any Adverse Events (AEs) including disclosures of harm, acute distress, or technology misuse will be monitored, documented, and reported to the responsible researcher within 24 h. AEs trigger immediate counselor escalation in accordance with institutional safeguarding policies; serious AEs are logged and reviewed by the school’s safeguarding lead. The AI system is structurally restricted from issuing behavioral directives; all guidance remains purely reflective and strictly under human counselor’s clinical oversight.

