Quantitatively, the design combines a within-subject trait-level pre–post comparison with an embedded single-case AB probe. The sequence consists of a pre-intervention baseline (Phase A; Weeks −2 and −1) and an active intervention period (Phase B; Weeks 1–8). The two-week baseline was adopted. A minimum of 10 data points in Phase A provides a more stable trend estimate for Tau-U baseline correction and more clearly distinguishes pre-existing directional drift from intervention-related change. Throughout Phase B, state-level EMA micro-ratings (1–7 Likert scales) index continuously index momentary regulation states. Trait-level self-regulation and social connectedness are measured at pre- and post-intervention timepoints via the within-subject standardized mean difference (Cohen’s *d*). To rigorously capture the dynamics of the state-level micro-trajectories, data will be evaluated using Tau-U, a robust, best-practice non-overlap effect size optimized for AB sequences in single-case experimental design (SCED) methodology.

The qualitative strand consists of (a) weekly counselor fidelity logs and (b) brief, one-sentence reflective student notes. These materials are not narrative interviews; rather, they serve as real-time process-evidence. Therefore, the analytic objective is not to achieve thematic saturation, but to execute mechanism-alignment detection. Reflexive thematic analysis will be used to identify and verify whether developmental practice indicators outlined in Table 1 occurred within a real-world educational environment.

All reflective notes remain accessible to the counselor to preserve the core ethical principle of human relational containment. The AI system does not store raw text beyond the generation of summary logs. Data retention adheres strictly minimal-retention feasibility norms; export functions are disabled. No participant data or conversational data is used for model training or model improvement. Furthermore, no algorithmic action is permitted without the possibility of immediate human override; should emotional dysregulation signals emerge, counselors escalate the case in accordance with established institutional safeguarding protocols. In this design, the AI is never the locus of clinical decision; rather, it is the engine for prompt density. Human counselors retain absolute safeguarding authority and interpretive control.

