#### AI system specification

Deployment uses a conversational Large Language Model (LLM) constrained to MI-style reflective prompts. Therefore, the following six aspects of the AI system are specified. (1) System architecture: the system is built on a hosted LLM API (e.g., GPT-4o or equivalent) accessed via a secure HTTPS endpoint. A structured prompt layer constrains all outputs to MI-style reflective responses; the model has no capacity to issue clinical directives. A school-side web application manages student authentication, prompt scheduling, and log aggregation. The counselor receives a read-only dashboard displaying aggregated weekly summaries. (2) Inference mechanisms: at each interaction, the system retrieves the student’s current weekly objective from the protocol schedule and selects a prompt template from the versioned library. No personalized inference or predictive modelling is performed; prompt selection is rule-based and fully deterministic, which eliminates black-box decision risk. (3) Data management: all prompt templates and micro-nudge libraries are hash-versioned to ensure reproducibility. Weekly interaction logs store only aggregated counts and engagement summaries (i.e., whether a prompt was opened and whether a note was submitted); raw conversational text is not retained beyond the session. Counselor fidelity logs are stored separately on the school’s own server and are not transmitted to the AI provider. (4) Privacy protection: the system is designed to comply with applicable data protection frameworks (e.g., GDPR, FERPA). No personally identifiable information is transmitted to the LLM API; each student is represented by a pseudonymous ID. Parental or guardian consent is required for all participants under 18. All data in transit are encrypted; data at rest are stored on school-controlled infrastructure. (5) Update procedures: prompt libraries and system instructions are updated only between academic cohorts, not during an active protocol cycle. Any update triggers a full version increment and requires sign-off by the research team prior to deployment, ensuring within-study consistency. (6) Algorithmic audit: prior to deployment, the full prompt library is reviewed by at least two independent raters for cultural sensitivity, developmental appropriateness, and potential for harmful outputs. Banned-topic filters and automated crisis keyword detection are evaluated against a benchmark set of at-risk phrases; any keyword match triggers an immediate handoff to the human counselor. Post-hoc audit logs are retained for the duration of the study to support independent review.

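### Two fixed delivery rules, the mid-cycle prompt freeze and the 24-hour lapse trigger, carry no safety exception to match the promise of immediate human override

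*Protocol article*

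**What the plan says.** **The promise.** Research design makes human override a condition of everything the system does: "no algorithmic action is permitted without the possibility of immediate human override". The same sentence goes on to say that counselors escalate under institutional safeguarding rules when signs of dysregulation appear.

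**Delivery.** Model definition sets out eight consecutive school weeks with daily nudges (Channel 1) and short micro-coaching dialogues (Channel 2). A dialogue starts when the student asks for one, or automatically after 24 hours without engagement.

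**The freeze.** AI system specification item (5) confines changes in prompt libraries and system instructions to the interval between academic cohorts. Each update needs a version increment and sign-off by the research team. Item (2) makes prompt selection rule-based and deterministic, and item (3) places the libraries under hash versioning.

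**Human routes.**
- Setting and participants: "AEs trigger immediate counselor escalation in accordance with institutional safeguarding policies".
- AI system specification item (6), on crisis keywords: "any keyword match triggers an immediate handoff to the human counselor". The same item says "Post-hoc audit logs are retained for the duration of the study to support independent review".
- AI system specification item (1): "The counselor receives a read-only dashboard displaying aggregated weekly summaries". Also in item (1): "A school-side web application manages student authentication, prompt scheduling, and log aggregation".
- Model definition: "counselors receive an auto-generated weekly summary", and "the counselor supervises fidelity, not content generation".
- Limitations: counselors review flagged interactions and must intervene at once on factually dubious output. They also step in when a student seems to be substituting the AI for people. Bias that survives the pre-deployment audit is to be documented.

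**The concern.** The override sentence is universal: it covers every algorithmic action and it says immediate. A rule that fixes system behaviour in advance should then say what happens when a human needs to interrupt it for safety. Two rules do not.

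First, the article accepts that biased prompts may pass the audit and that inappropriate output cannot be fully excluded, yet its update rule leaves no way to remove a faulty template while students are receiving it. Second, the lapse trigger treats 24 hours of silence as disengagement to be answered with an automated dialogue. A student just escalated for distress may well go silent, and that is when an unprompted automated dialogue is least wanted.

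Participants are 14 to 18, with guardian consent required below 18. The article offers itself as a protocol that later trials can adopt directly, so a site that follows these rules to the letter would inherit both gaps.

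**Working it through.** No sample size, power, error rate or event rate enters this point, so there is nothing to recompute. The check sets the rules beside the promise and follows each to its result.

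**Case 1: a template is found harmful or biased during a cycle.**
1. Selection is deterministic (item 2), so the template is sent whenever the schedule calls for it.
2. The libraries are hash-versioned (item 3), so taking a template out is naturally read as a library change.
3. Library changes wait until the cohort ends (item 5). No safety exception is given.
4. For residual bias, Limitations states documentation. For factually dubious output it states immediate intervention, but it does not say that this may alter the library.
5. Result: under the text as written, the template stays in the schedule. The freeze covers at least the 8 delivery weeks. A fault recognised at the end of week 2 leaves 8 − 2 = 6 weeks of frozen content. That is an upper bound on exposure. A nudge tied to one weekly theme is sent only while that theme is current, whereas a faulty system instruction could apply in every remaining week.

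**Case 2: a student is escalated or handed off.**
1. An adverse event triggers counselor escalation (Setting and participants), or a keyword match triggers handoff (item 6).
2. Neither rule says what happens afterwards to scheduled nudges or to the lapse trigger.
3. The student stops engaging for 24 hours.
4. The lapse rule (Model definition) has no exception for this student, so Channel 2 opens an automated dialogue.
5. Result: followed exactly, the rules send automated contact to a student already transferred to human care.

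**Does another described route close either gap?**
- The dashboard is read-only and weekly, so it does not supply an immediate stop.
- The audit logs are post hoc.
- The keyword handoff is immediate, but it covers only keyword matches and says nothing about later delivery.
- Escalation and the duties in Limitations act on the student's case or on a flagged output. Neither is described as suspending delivery.
- The school-side application manages scheduling, so it is the natural place for a pause. The text neither describes one there nor rules one out.

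**The case against.** A reader might infer a direct contradiction: override is promised, the counselor has only a read-only weekly dashboard, so override is impossible. The documents do not support that. The dashboard is never called the only interface, nor the counselor the only person able to intervene. Scheduling sits in a school-side application, where an administrator could hold a stop control. The remark about content generation concerns who writes prompts, not who can halt them. How a pause is operated is detail that a condensed article may leave to the full protocol. All of this stands. The dashboard shows only that the one counselor interface described does not supply the override.

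It can also be argued that the override sentence, read whole, places authority with humans and refers to institutional procedures that are not shown. That is fair, and those procedures may well suspend delivery. It does not change what the lapse rule says in this document.

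On the freeze, suspending delivery to a student is not a library update, and item (5) has a sound purpose: consistency within a study. Both points hold, and the freeze does not itself contradict the override sentence. But pausing one student does not remove a faulty template for the others, and a rule that states when updates are allowed, without a safety exception, is a choice made in this document.

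Finally, risk is reduced beforehand: students in acute crisis are not enrolled, participation is voluntary, and at least two raters review the library. This limits the size of the point without removing it, since Limitations itself says bias may remain.

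**Conclusion.** The point holds in limited form. Two stated rules, followed exactly, fit poorly with the article's own override condition: content found harmful cannot be withdrawn mid-cycle, and silence after escalation can start an automated dialogue. It is a minor safety-consistency point. It affects no estimate, confidence interval or feasibility threshold, and no risk of harm can be given because the article reports no event rates.

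The conclusion assumes that removing a template counts as a library update, and that no unshown document suspends delivery after escalation. If the full protocol already contains such exceptions, the article only needs to say so.

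**What to change.** 1. **AI system specification, item (5).** Allow a template or system instruction to be disabled, but not rewritten, during a cycle for safety reasons, with a version increment and a log entry.
2. **AI system specification, item (1).** State that escalation or keyword handoff suspends both channels for that student, including the 24-hour lapse trigger, through a time-stamped pause in the school-side scheduling application. The investigators and the safeguarding lead should set the criteria for resuming.
3. **If neither is built,** narrow the override sentence in Research design to the safeguards that exist.

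The text changes are a few sentences. If no pause exists, one must be added to an application that already handles scheduling; the article does not describe the software closely enough to cost that. Outcomes and analysis are unchanged. The downside is slightly non-uniform delivery within a cohort, which the version log and pause time stamps would document. The pause does not help a student whose crisis has not yet been recognised.

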#### AI system specification

Deployment uses a conversational Large Language Model (LLM) constrained to MI-style reflective prompts. Therefore, the following six aspects of the AI system are specified. (1) System architecture: the system is built on a hosted LLM API (e.g., GPT-4o or equivalent) accessed via a secure HTTPS endpoint. A structured prompt layer constrains all outputs to MI-style reflective responses; the model has no capacity to issue clinical directives. A school-side web application manages student authentication, prompt scheduling, and log aggregation. The counselor receives a read-only dashboard displaying aggregated weekly summaries. (2) Inference mechanisms: at each interaction, the system retrieves the student’s current weekly objective from the protocol schedule and selects a prompt template from the versioned library. No personalized inference or predictive modelling is performed; prompt selection is rule-based and fully deterministic, which eliminates black-box decision risk. (3) Data management: all prompt templates and micro-nudge libraries are hash-versioned to ensure reproducibility. Weekly interaction logs store only aggregated counts and engagement summaries (i.e., whether a prompt was opened and whether a note was submitted); raw conversational text is not retained beyond the session. Counselor fidelity logs are stored separately on the school’s own server and are not transmitted to the AI provider. (4) Privacy protection: the system is designed to comply with applicable data protection frameworks (e.g., GDPR, FERPA). No personally identifiable information is transmitted to the LLM API; each student is represented by a pseudonymous ID. Parental or guardian consent is required for all participants under 18. All data in transit are encrypted; data at rest are stored on school-controlled infrastructure. (5) Update procedures: prompt libraries and system instructions are updated only between academic cohorts, not during an active protocol cycle. Any update triggers a full version increment and requires sign-off by the research team prior to deployment, ensuring within-study consistency. (6) Algorithmic audit: prior to deployment, the full prompt library is reviewed by at least two independent raters for cultural sensitivity, developmental appropriateness, and potential for harmful outputs. Banned-topic filters and automated crisis keyword detection are evaluated against a benchmark set of at-risk phrases; any keyword match triggers an immediate handoff to the human counselor. Post-hoc audit logs are retained for the duration of the study to support independent review.

To ensure flexibility and continuity of engagement, students access the AI micro-nudge system using their own personal devices (e.g., mobile phones, tablets, or home computers). To uphold digital equity, school terminals remain accessible as an alternative for students without personal access. The platform also integrates comprehensive accessibility features including screen-reader compatibility, high-contrast text options, and optional multilingual delivery to support equitable participation.

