### Model definition

The model is conceptualized as a developmental delivery architecture wherein human counselors establish the relational frame and developmental arc, while AI system executes the high-frequency micro-dosage required for proximal skill enactment. Critically, this intervention does not conceptualize AI as a counselor analog, therapist substitute, or diagnostic component, but as a systemic dosage amplifier. Counselors maintain primary responsibility for relational containment, while the AI autonomously delivers the high-volume, micro–developmental practice opportunities that human counselors cannot feasibly scale. This approach is grounded in the developmental reality that self-regulation and social connectedness are not cultivated through episodic learning, but through continuous, real-world repetition. The architecture therefore mirrors the mechanisms of motor-skill acquisition: micro-practice → consolidation → transfer. This counselor–AI co-delivery framework makes this repetition feasible within standard school constraints.

The intervention is deployed throughout eight consecutive school weeks. Each week focuses on one thematic developmental objective (see Table 1) and offers a synchronous 10–15-min counselor mini-session. This mini session serves as a vital “anchor point,” grounding the week’s developmental target in a supportive relational context while allowing the counselor to check ecological fit, safety, and progress. The remainder of the weekly dosage is delivered digitally through daily MI-style micro-nudges (e.g., ≤ 40 words). The sequence is intentionally graded to build capacity over time: initial weeks emphasize foundational awareness and micro-choice recognition; intermediate weeks prioritize active skill application in real-life contexts; final weeks focus on value mapping, identity congruence, and future transfer. In essence, the intervention is paced not by superficial “topic rotation,” but through the cumulative scaffolding of practice complexity.

**Table 1 tab1:** Structured eight-week progression of developmental objectives and measurable indicators.

Week	Theme	Weekly skill focus	Measurable outcome wording	Measurement schedule
0				Weeks −2 to −1: Consent, demographics, BSCS/SSBS (pre), two-week daily EMA baseline (Phase A)
1	Awareness	Noticing internal states & situational triggers	Student(s) can label at least one emotional state + one situational trigger per day	

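### Counselors are to review flagged AI interactions, but the retention rule discards the dialogue text with no exception for flagged sessions

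*Protocol article*

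**What the plan says.** Four parts of the protocol article bear on this point.

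- **Review duty (Limitations).** The article accepts that a language model can produce inaccurate or unsuitable responses and that the prompt constraints cannot remove this risk. Counselors are therefore to review flagged interactions and to treat factually doubtful AI output as a fidelity problem calling for immediate action. What sets a flag is not stated.
- **Retention (AI system specification, item 3).** "Weekly interaction logs store only aggregated counts and engagement summaries", explained as whether a prompt was opened and whether a note was submitted. Also, "raw conversational text is not retained beyond the session".
- **Retention again (Research design).** "The AI system does not store raw text beyond the generation of summary logs".
- **What reaches the counselor (AI system specification, items 1 and 6).** "The counselor receives a read-only dashboard displaying aggregated weekly summaries". In addition, "any keyword match triggers an immediate handoff to the human counselor". Audit logs are kept for the length of the study for independent review; their content is not described.

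**The concern.** The plan gives counselors a task and, by a separate rule, removes the material needed to carry it out. Judging whether a model's reply was inaccurate or unsuitable means reading the reply, and usually the student's message before it. A count showing that a dialogue took place does not help.

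This review is the human check that the article sets against a risk it says it cannot eliminate, in a study of students aged 14 to 18. If the text is gone when the counselor looks, the check exists only on paper. The article also presents itself as a research-ready protocol for later randomized trials, so the mismatch could be copied into them.

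**Working it through.** No sample size, power or event-rate calculation bears on this point. The check was to trace every stated source from which a counselor could read the text of a flagged dialogue once the session is over.

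| Stated source | Where | Gives the text of a flagged session afterwards? |
|---|---|---|
| Weekly interaction logs | AI system specification (3) | No. Counts and engagement summaries only |
| Counselor dashboard | AI system specification (1) | No. Read-only aggregated weekly summaries |
| Weekly auto-generated summary | Model definition | No. It lists nudge engagement, micro-coaching activity and note submissions; under item (3) there is no stored dialogue content to show |
| Raw dialogue text | AI system specification (3) | No. Not kept after the session; no exception stated |
| Raw dialogue text | Research design | No. Not kept once summary logs exist; no exception stated |
| Keyword handoff | AI system specification (6) | Not stated. It might expose the live session, for keyword matches only |
| Audit logs | AI system specification (6) | Not stated. Meant for independent review; holding dialogue text there would conflict with item (3) |
| Reflective notes | Research design | No. Open to the counselor, but they are one-sentence student notes and not the dialogue |

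Three things follow.

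1. **No source is said to hold the text.** The two that are left open, the handoff and the audit logs, do not settle the matter. The handoff covers keyword matches during a session. The audit logs could hold dialogue text only by breaching the retention rule.
2. **The two deletion points differ.** Item (3) ends retention with the session. Research design ends it when summary logs are generated, and those logs are weekly. If generation means the weekly run, text could exist for days under one sentence and not at all under the other. Neither sentence gives the counselor access to it.
3. **The trigger is undefined.** Keyword detection and banned-topic filters are described in item (6), but the article does not say whether either of them sets the flag meant in Limitations. Without a trigger, no one can say which sessions would need an exception.

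The only exposure figure the article supports is access to the micro-coaching channel: 40 × 8 = 320 to 60 × 8 = 480 student-weeks at full retention. This is not a count of dialogues, flags or missed cases.

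**The case against.** **The article is condensed.** Dashboard fields, keyword lists and escalation steps usually sit in a fuller document, and their absence here is no fault. That stands for those details. It does not dispose of this point, because the retention rule is stated outright. A fuller document could give counselors past text only by adding the exception that item (3) lacks.

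**Deletion after the session need not block review during it.** Text exists while the session runs, and a keyword handoff is immediate, so a counselor might read it live. This is possible for keyword matches. It is not stated, and it does not cover interactions flagged for doubtful AI output and looked at later.

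**A stronger reading is tempting:** that distress voiced in a dialogue without a keyword match has no route to the counselor, and that this is an error in the plan. The article does not support it.

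- Not giving counselors routine sight of dialogues fits the plan's stated minimal-retention and data-protection approach for minors.
- There are backstops. "All reflective notes remain accessible to the counselor", and the weekly session has a safety purpose, "allowing the counselor to check ecological fit, safety, and progress".
- Students with acute crisis indicators are not enrolled. Algorithmic actions must be open to immediate human override.
- The escalation duty, "should emotional dysregulation signals emerge, counselors escalate the case in accordance with established institutional safeguarding protocols", does not require counselors to read every dialogue.
- Limitations mentions socially isolated or distressed students as at risk of emotional dependence on the AI, not of undetected distress. The sample dialogue in Appendix C, about being ignored at break, is ordinary peer content of the kind the programme is meant to work with.

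It remains true that distress voiced only in an unmatched dialogue reaches the counselor only if the student raises it again. That is a limit of a deliberate trade-off, which the sponsor may wish to narrow.

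**Conclusion.** The point holds in its narrow form. The duty to review flagged interactions and the rule on raw text cannot both be followed once a session has ended, and the two retention sentences disagree about when deletion occurs. This should be corrected before deployment because it disables a safety check that the article relies on.

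Its size cannot be given. The article reports no flag rate, no rate of doubtful output and no sensitivity for keyword detection, and the student-weeks above measure access only. Feasibility thresholds, effect estimates and the analysis are unaffected.

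The conclusion assumes that review takes place at least partly after the session and that the audit logs respect the retention rule. If the full protocol already keeps flagged text for review, only the article's wording needs correcting.

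**What to change.** 1. **AI system specification (3).** Keep the retention sentence and add: *The exception is a session that was keyword-matched or flagged. Its text is kept on the school-controlled server until the counselor has reviewed it, within 24 h, and is then deleted.* The 24 h is a suggestion that matches the adverse-event reporting window in Setting and participants.
2. **AI system specification (6).** Say what sets a flag: a keyword or banned-topic filter match during the session, or the student.
3. **Research design.** Align the raw-text sentence with item (3), so that there is one deletion point and one exception.
4. **Optional.** Add to each micro-coaching dialogue a fixed choice to ask for counselor follow-up, which sets the flag and alerts the counselor. This gives distress that matches no keyword a route, but only if the student uses it. Since students may be on home devices, the option should say until what hour alerts are read the same day.

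**Cost.** Steps 1 to 3 need a few sentences of text and a small storage rule. A limited amount of sensitive text from minors would be held briefly, which the consent text should name. Counselors would have flagged sessions to read within a day, plus some alerts if step 4 is adopted. Doubtful output that trips no filter and that the student does not flag would still go unreviewed, and the plan should say so.
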